## Abstract

**Background:**

Hypertension is a major risk factor for cardiovascular disease, and its control rate has remained low worldwide. Studies have found that telemonitoring blood pressure (BP) helped control hypertension in randomized controlled trials. However, little is known about its effect in a structured primary care model in which primary care physicians (PCPs) are partnering with cardiology specialists in electronic healthcare data sharing and medical interventions. This study aims to identify the effects of a coordinated PCP-cardiologist model that applies telemedicine tools to facilitate community hypertension control in China.

**Methods/design:**

Patients with hypertension receiving care at four community healthcare centers that are academically affiliated to Shanghai Chest Hospital, Shanghai JiaoTong University are eligible if they have had uncontrolled BP in the previous 3 months and access to mobile Internet. Study subjects are randomly assigned to three interventional groups: (1) usual care; (2) home-based BP telemonitor with embedded Global System for Mobile Communications (GSM) module and unlimited data plan, an app to access personal healthcare record and receive personalized lifestyle coaching contents, and proficiency training of their use; or (3) this plus coordinated PCP-cardiologist care in which PCPs and cardiologists share data via a secure CareLinker website to determine interventional approaches. The primary outcome is mean change in systolic blood pressure over a 12-month period. Secondary outcomes are changes of diastolic blood pressure, HbA1C, blood lipids, and medication adherence measured by the eight-item Morisky Medication Adherence Scale.

**Discussion:**

This study will determine whether a coordinated PCP-Cardiologist Telemedicine Model that incorporates the latest telemedicine technologies will improve hypertension care. Success of the model would help streamline the present community healthcare processes and impact a greater number of patients with uncontrolled hypertension.

**Trial registration:**

ClinicalTrials.gov, NCT02919033. Registered on 23 September 2016.

**Electronic supplementary material:**

The online version of this article (doi:10.1186/s13063-017-1970-z) contains supplementary material, which is available to authorized users.

## Background

Hypertension is one of the major causes of death globally and affects more than 20% of the adult population in China, according to the latest statistics [1]. Multiple lines of evidence have suggested that lowering blood pressure (BP) with anti-hypertensive medications and a more healthful lifestyle would decrease mortality and disability from severe complications [2–4]. However, hypertension remains inadequately treated through routine provider visits and patient self-management. In China, the majority of hypertension care is provided by primary care physicians (PCPs) in community practices. The imbalance between the small number of available PCPs and the vast number of patients has limited the average PCP visit to less than 9 minutes. Hypertension-specific assessments such as reviewing BP trends, ocular exams, and renal function tests are not often performed, and education about medication adherence and behavioral changes may not be provided as necessary.

The advent of mobile healthcare technologies and telemedicine systems has demonstrated tremendous potential to improve the effect of chronic disease management of hypertension, diabetes, cardiac disorders, and respiratory diseases [5–9]. A recent meta-analysis indicated that blood pressure telemonitoring could reduce systolic blood pressure (SBP) by 4.7 mm Hg and diastolic blood pressure (DBP) by 2.5 mm Hg, with an increased hypertension control rate [10, 11]. In diabetic care, a more robust app-based glycemic control algorithm has proven effective in reducing HbA1C by 1.9% in cluster-randomized trials [9, 12–14]. These beneficial effects are considered to result from enhanced disease awareness, self-management, and patient engagement by healthcare professionals [15–18]. It is therefore conceivable that broader implementation of telemedicine systems may help restore the balance of supply and demand in community hypertension care services by mobilizing patient involvement and improving provider’s efficiency.

To combat the growing public health challenge of hypertension, regulators in Shanghai, China are piloting a novel community healthcare PCP-Cardiologist Telemedicine Model (PCTM) in which PCPs are collaborating more closely with cardiologists of larger comprehensive hospitals by leveraging a telemedicine system that integrates remote BP monitoring with healthcare decision support engines. The present paper describes a three-arm randomized controlled trial (RCT) to evaluate the effectiveness of this model in which BP data and personal healthcare information are collected, stored, and displayed by a mobile app in sync with the cloud engine, and personalized healthcare delivery can be provided in a proactive and preventive way by the joint effort of PCPs and cardiologists. By comparing the BP control outcomes of (1) usual care, (2) patient self-management using telemedicine tools, and (3) the PCTM, which includes the coordinated cardiologist services plus the same set of telemedicine tools, we will be able to draw more precise conclusions about this PCTM in hypertension management and determine whether a similar model should be developed for other chronic conditions. Furthermore, as our previous study conducted in more than 3000 retail pharmacies has implicated that improved medication compliance might be the main mechanism underling better BP control, we will perform a Morisky analysis to identify the correlation between medication adherence and the effect of hypertension care in this trial [19, 20].

## Methods/design

### Study design

The coordinated PCTM study is a 12-month, pragmatic three-arm trial aiming to compare two telemedicine-based hypertension interventions with usual care. Group 1 participants receive usual care (UC) that complies with China’s Hypertension Prevention and Treatment Guideline 2010 (the national guideline) [21]. Group 2 patients additionally receive a BP telemedicine system including a BP telemonitor and a mobile app. Group 3 participants receive all of the above plus coordinated services jointly provided by their PCPs and a designated team of cardiologists who have access to the secure CareLinker website and review patient data with PCPs once every 3 months. PCP-directed proactive interventions such as phone consultations, requests for an immediate clinic visit, or referrals may also be given to Group 3 participants if their relevant PCP receives alerts produced by the CareLinker cloud engine as a result of detecting abnormal BP variability. A total of 330 enrolled patients will be randomized to each group in a 1:1:1 allocation ratio, and all outcome measures will be assessed at baseline (T1), 6 months (T2), and 12 months (T3) throughout the study duration (Fig. 1). We hypothesize that timely healthcare information exchange and closer collaboration between PCPs and cardiologists will improve community BP control. The Standard Protocol Items: Recommendations for Interventional Trials (SPIRIT) checklist is presented in Additional file 1 [22].

**Fig. 1 Fig1:**
[figure not shown]
Study design of the coordinated PCP-Cardiologist Telemedicine Model (PCTM)

### Setting

This study will be taking place in the XuHui District in Shanghai, China. The four participating community healthcare centers (CHCs) are classified as tier 1 clinics; each has approximately 30–40 practicing PCPs, and they provide a full range of primary care services to nearly 330,000 residents in total. Cardiologists are mainly recruited from Shanghai Chest Hospital, which is located in the same district and is one of the largest chest specialty hospitals in the nation. Potentially eligible patients are identified and referred by PCPs from CHCs, where all data collection will be conducted including baseline and follow-up tests, except for home-based BP telemonitoring.

### Eligibility: inclusion and exclusion criteria for patients

Inclusion criteria of the trial are as follows: (1) age 21 years or older; (2) a clinical diagnosis of hypertension with uncontrolled BP in the previous 3 months, and currently taking or about to take anti-hypertensive medications; (3) received high school or higher level of education; (4) active user of smart phone (Android or Apple) and mobile apps; (5) the average of three BP measurements during the screening visit at the CHC is ≥140/90 mm Hg, or ≥130/80 mm Hg if the patient has diabetes or renal disease; (6) the ability to give informed consent.

Medical exclusion criteria include the following: acute coronary syndrome, heart failure, cardiac arrhythmia, stroke within the past 3 months, renal failure, cancer, dementia, severe or acute psychiatric illness, pregnancy or intention to be pregnant in the next 18 months, and hospitalization within 3 months. Additional exclusion criteria include participation in another clinical trial, arm circumference >32 cm (this may affect the accuracy of BP measurement due to the cuff size limit of the telemonitor), and unwillingness to comply with the 12 months intervention duration.

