#### Secondary outcomes

The key secondary endpoints are changes in mean DBP and hypertension control rate defined as BP <140/90 mm Hg or <130/80 mm Hg (for patients with diabetes or renal diseases) following the national guidelines [21] and changes in measures related to hypertension complications (HbA1C, body mass index (BMI), and lipid levels) from baseline (T1) to 6 months (T2) and 12 months (T3). The other secondary outcome is anti-hypertensive medication adherence, which is assessed by the self-reported, eight-item Morisky Medication Adherence Scale (MMAS) modified to focus on BP drugs at baseline (T1) and 12 months (T3) [20]. These outcomes are measured for the three study groups and compared between the control and intervention groups.

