### Randomization process

We use a block randomization design to ensure balance within CHCs and baseline SBP measurements. We set each CHC as a block, and patients are randomized to three groups in each block with a rate of 1:1:1. A study statistician is solely responsible for generating the randomized allocation sequence using computer software (MATLAB version 2014a) and assigning patients to the intervention or control groups. The allocation sequence is concealed in opaque envelopes from all study researchers until the interventions are assigned. Furthermore, an engineer from CareLinker who does not know the grouping information is in charge of training participants of Groups 2 and 3 to use the BP telemonitor and app in order to ensure an equal level of training between the two intervention groups. Due to the nature of the intervention, the study is an open-label trial to all participating patients, physicians, and coordinators at each site.

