Baseline data will be analyzed and presented using numerical summaries and graphical illustrations. We will perform *F* tests for continuous variables and Pearson’s chi-square tests for categorical variables to assess the difference of baseline characteristics among the three groups. To analyze the primary outcome, we will use a linear mixed model to identify the effectiveness while adjusting the baseline using the following covariates as appropriate: baseline SBP, age, gender, BMI, education levels, exercise, drinking patterns, tobacco use, and CHCs. Only those covariates found to be statistically significant to the outcomes will be selected as explanatory variables for inclusion in the final model. All statistical tests are performed using *F* tests. We intend to use Fisher’s protected least significant difference (LSD) method to protect against multiple comparisons, followed by pairwise comparisons between study groups only if the overall *F* test is significant. The secondary endpoints of DBP, HbA1C, blood lipid levels, and medication adherence will be determined separately between baseline and the follow-up time points for patients of the three study arms. The analytical approach will be identical to those described in the above section for primary outcome analysis.

Missing data will be assumed to be missing at random; therefore, the linear mixed model has already accounted for this assumption. We will use multiple imputation methods to analyze the missing data.

We will also carry out subgroup analyses of the primary and secondary outcomes stratified by the following characteristics at baseline: BMI (<24, ≥24), hypertension stage (stage1, stage 2, and stage 3), education level (non-college, college, or above), presence of one or more comorbidities, and self-reported medication adherence. No formal interim analysis of the primary and secondary outcomes is planned, but progress reports will be prepared and presented to PCPs and partnering cardiologists every 3 months.

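### Treatment status at entry (on drugs or about to start) is missing from the candidate covariates, and the baseline adherence score probably does not apply to patients not yet on blood pressure drugs

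*Protocol article*

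**What the plan says.** Inclusion criterion 2 (Eligibility) accepts patients with uncontrolled hypertension who are "currently taking or about to take anti-hypertensive medications". Two kinds of patient therefore enter, and which kind each is has to be established at screening.

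The section on statistical hypothesis, methods and analyses names the candidates for the primary linear mixed model: "baseline SBP, age, gender, BMI, education levels, exercise, drinking patterns, tobacco use, and CHCs". Selection works within that list: "Only those covariates found to be statistically significant to the outcomes will be selected as explanatory variables". Treatment status is not on it, nor among the subgroup factors. Randomization aims at other factors: "We use a block randomization design to ensure balance within CHCs and baseline SBP measurements".

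Adherence is a secondary outcome, and the Abstract describes it as a change. The instrument is the "eight-item Morisky Medication Adherence Scale (MMAS) modified to focus on BP drugs at baseline (T1) and 12 months (T3"). The analysis section says that "medication adherence will be determined separately between baseline and the follow-up time points for patients of the three study arms", by the same approach as the primary outcome. Self-reported adherence at baseline is also a subgroup factor for the primary and secondary outcomes. For gaps in the data, the article assumes missing at random and adds: "We will use multiple imputation methods to analyze the missing data".

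**The concern.** Starting a first antihypertensive drug could plausibly be a strong determinant of 12-month SBP change. The eligibility criterion itself splits the population on this, yet the plan names exercise, drinking and tobacco use as candidates and leaves it out. Since final covariates come only from the stated list, it could not enter the model as planned.

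The adherence problem is of another kind. A questionnaire about taking BP drugs has no obvious answer from someone who is not taking any. The article does not say how such a patient is scored at T1, how change from T1 is formed, or which baseline-adherence subgroup the patient joins. The one general rule that could reach the gap is multiple imputation under missing at random. Applied here, it would create an adherence score for drugs the patient was not taking; without it, the patient drops out of the change analysis and the subgroup. This matters because the Background section presents better adherence as a possible main mechanism of BP control and makes its correlation with the effect of care an aim of the trial.

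**Working it through.** **1. The plan's own figure.** Inputs from the sample size section: SBP difference 7, SD of change 16.5, two-sided 5%, power 80%, dropout 20%.

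- SBP: n = 2 × (1.960 + 0.842)² × (16.5/7)² = 87.2, rounded up to 88 per group.
- DBP (difference 5, SD 11.5): n = 83.0, rounded up to 84, so SBP governs.
- Dropout: 88/0.8 = 110 per group, and 3 × 110 = 330.

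The stated figures reproduce. There is no arithmetic error.

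**2. How much status could explain.** The article gives neither the share of new starters, p, nor their extra SBP fall, d. I assume p = 5-30% and d = 5-15 mm Hg. The variance due to status is p(1−p)d², and the variance of change is 16.5² = 272.25. Power at 88 per group is Φ(7/(SD × √(2/88)) − 1.96), which gives 80.3% at SD 16.5 (79.9% by the noncentral t).

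The article does not say whether 16.5 describes the mixed population (reading A: adjustment lowers the SD) or patients of like status (reading B: the unadjusted SD is larger).

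| p | d | Share of variance (p(1−p)d²/272.25) | A: adjusted SD, power at 88 | B: unadjusted SD, power at 88 |
|---|---|---|---|---|
| 5% | 5 | 1.19/272.25 = 0.4% | 16.46, 80.5% | 16.54, 80.2% |
| 5% | 15 | 10.69/272.25 = 3.9% | 16.17, 81.9% | 16.82, 78.8% |
| 20% | 10 | 16.0/272.25 = 5.9% | 16.01, 82.7% | 16.98, 78.1% |
| 30% | 5 | 5.25/272.25 = 1.9% | 16.34, 81.1% | 16.66, 79.6% |
| 30% | 15 | 47.25/272.25 = 17.4% | 15.00, 87.2% | 17.87, 73.8% |

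These are upper figures for what status adds, because baseline SBP and the other candidates may already absorb part of it.

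**3. Chance imbalance.** At p = 20% and d = 10, imbalance in new starters between two arms of 88 moves the unadjusted difference by up to 1.96 × √(2 × 0.2 × 0.8/88) × 10 = ±1.18 mm Hg (95% range). Under reading A the unadjusted 95% half-width is 1.96 × 16.5 × √(2/88) = 4.87, and the adjusted one is 1.96 × 16.01 × √(2/88) = 4.73. Since 4.73² + 1.18² = 23.8 = 4.87², the imbalance is one component of the existing interval and not an addition to it.

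**4. Adherence.** If the T1 scale does not apply to new starters, the number affected is 110p per arm: 5.5 at 5%, 22 at 20% and 33 at 30%. Over all 330 patients this is about 17 to 99. Whether a T1 score applies follows from treatment status at entry, so the gap is structural. Imputation under missing at random presupposes a true value that happened not to be observed; here there is probably none.

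**The case against.** For SBP the case against is strong, and most of it stands.

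- A reader might infer that the omission biases Group 3 against Group 1. Patients are randomized 1:1:1 within each CHC, so it does not.
- A reader might treat the ±1.18 mm Hg as an extra error in the result. Step 3 shows that it already lies inside the confidence interval.
- The trial has its planned power under reading A, so what is lost is an optional gain.
- Both p and d are assumptions. The recruitment section describes registered patients already receiving regular community care, and usual care includes prescription refills and medication adjustment. New starters may be few, and treated patients may also have their drugs changed.

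On adherence, the absence of a T1 score is an inference from the scale's focus. A patient about to start may have used such drugs before and answer about that use. Nor does the article say that a non-applicable score counts as missing, so imputing it is a possible reading and not a stated intention.

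It can also be said that scoring rules belong in the SAP that the article promises before database lock. That holds for the detail. But the article itself fixes the covariate list, the selection rule, the baseline comparison, the adherence subgroup and the missing-data method, and these stated choices do not fit its own eligibility criterion.

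**Conclusion.** The point holds in two parts of unequal weight.

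For SBP and DBP it is minor: a baseline factor fixed by the eligibility criterion is left unused. On the assumed ranges it explains about 0.4-17% of the variance of SBP change before overlap with other covariates, and the low end is plausible. The documents do not support a claim of bias, of a wrong sample size, or of an error beyond the confidence interval.

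For the adherence outcome and its subgroup it is moderate. The baseline is probably not applicable to patients not yet on BP drugs, and the only stated remedy does not suit such a value. This rests on reading the scale as concerning current drug use. The number affected depends on a share that the article does not give. The documents do not show that scores will in fact be invented or patients lost; they leave both possible.

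**What to change.** 1. Record treatment status at T1 (on drugs or about to start). Prespecify it as a covariate in the SBP and DBP models, kept whether or not it is significant.
2. Make the main adherence analysis the comparison between arms at T3, with treatment status as a covariate. Use the baseline score only where it applies, for example as a term that acts only in patients on drugs at T1.
3. State that T1 adherence is not imputed for patients not on BP drugs. Keep multiple imputation for scores that apply but were not obtained.
4. In the baseline-adherence subgroup analysis, make patients not on BP drugs at T1 their own category.

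The cost is one degree of freedom in each model and changes to the analysis wording. Status is established when criterion 2 is checked, so no visit, test or sample size changes.

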### Withdrawal

Withdrawal criteria include the following: (1) the participant intends to drop out of the study; (2) the participant is unwilling to follow the study protocol such as not visiting the clinic as scheduled or having the lab tests performed; (3) the participant is withdrawn due to critical medical reasons. For patients who withdraw from the study, we will obtain a consent form to retrieve data directly from their electronic healthcare records (EHRs) in the CHCs and compare their outcome indicators with those from the patients who complete the study.

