### Outcomes

#### Primary outcome measures

The primary endpoint of the trial is changes in mean SBP from baseline (T1) to 12 months (T3) measured using the BP telemonitor (Bliss BL928). The 12 months BP readings will be determined by taking the average of three BP measurements at the follow-up visit to the CHC. All BP data are collected and uploaded simultaneously to the trial database.

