### Sample size and power calculation

The sample size required for this RCT is 330 patients based on the following assumptions. The RCT is powered to detect a clinically meaningful difference in average change between baseline and 12 months SBP of 7 mm Hg and DBP of 5 mm Hg between Group 1and Group 3. We assume that the standard deviation for difference in SBP from baseline to 12 months is 16.5 mm Hg and the difference in DBP from baseline to 12 months is 11.5 mm Hg. Using a two-sample comparison of the mean change between Group 1 and Group 3, a sample size of 88 patients per group is required to have 80% power at the 95% confidence level. This number is further adjusted to 110 per group to account for an estimated dropout rate of 20% during the 12 months follow-up. To reduce this potential dropout, we will provide all participants an additional 2 years of free health consultation services from PCPs and cardiologists as an incentive after they complete the trial. All analyses will be performed according to the intention-to-treat (ITT) principle.

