We also acknowledge limitations in this study. First, this is an open-label trial, as both patients and physicians are aware of the grouping information. Patient bias, especially for those in the control group, may occur when they are not compliant with follow-up clinic visits and even choose to discontinue the participation, while physician bias may occur when they provide interventions to the test group patients. We attempt to address this issue through intensive training of participating physicians and research nurses prior to the beginning of this study, and by setting up a project management team to continuously oversee the study progress to ensure that the protocol is being properly followed. Second, the recruited patients may reflect only a subpopulation who are frequent users of smart phones and mobile apps. Their demographic and healthcare profile may be distinctive from the rest of the hypertensive population, who are of different ages, at different geographic locations, and have less access to the Internet. Finally, the present study only involves four CHCs and one university hospital in Shanghai; thus, the findings and the PCTM model under study may not be generalized to other regions in China.

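### Withdrawal criterion (2) can end follow-up of patients who would still give a 12-month blood pressure, and the health-record back-up does not recover their primary outcome

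*Protocol article*

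**What the plan says.** The Withdrawal section of the protocol article gives three grounds: (1) the participant wants to leave; (2) "the participant is unwilling to follow the study protocol such as not visiting the clinic as scheduled or having the lab tests performed"; (3) critical medical reasons. For those who withdraw, it says "we will obtain a consent form to retrieve data directly from their electronic healthcare records (EHRs) in the CHCs" and that the investigators will "compare their outcome indicators with those from the patients who complete the study". It gives no other use for these data.

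The primary endpoint depends on a clinic attendance. Under Primary outcome measures: "The 12 months BP readings will be determined by taking the average of three BP measurements at the follow-up visit to the CHC".

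Under Sample size and power calculation: "All analyses will be performed according to the intention-to-treat (ITT) principle". The section on statistical hypothesis, methods and analyses repeats this for the primary analysis and adds that every effort will be made to have full data on each patient. On gaps in the data it says: "Missing data will be assumed to be missing at random; therefore, the linear mixed model has already accounted for this assumption". Multiple imputation is then added, and a full SAP is promised before database lock.

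The Discussion names a risk of this open-label design: "Patient bias, especially for those in the control group, may occur when they are not compliant with follow-up clinic visits". It adds that such patients might leave the trial, and answers with training and oversight.

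**The concern.** Criterion (2) stands apart from the patient's own wish to leave, so it can apply to someone who has not asked to stop. It also covers laboratory tests, which serve secondary outcomes only. As written, a patient who declines HbA1C or lipid tests, or who skips the 6-month visit, meets the criterion even if that patient would come for the 12-month BP. Ending study follow-up then turns an obtainable primary outcome into a missing one.

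At stake are precision and, under some conditions, bias in the Group 3 versus Group 1 comparison. A later SAP can choose how to model missing values, but it cannot recover readings that were never taken.

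**Working it through.** **The plan's own figures.** Inputs from Sample size and power calculation: difference 7 mm Hg, SD of change 16.5 mm Hg, 80% power, two-sided 5%, 20% dropout.

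- n per group = 2 × (1.96 + 0.84)² × 16.5² / 7², about 88, as stated.
- 88 / (1 − 0.20) = 110 per group, and 3 × 110 = 330, as stated.
- Planned loss: 330 × 0.20 = 66 patients, 22 per group. It is split neither by arm nor by reason, so the share due to criterion (2) is unknown.

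**Whom the criterion affects.**

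- Patients who refuse all visits have no 12-month reading with or without criterion (2). Nothing is lost by the rule.
- Patients who miss the 6-month visit or refuse tests, but would attend at 12 months, lose the primary outcome only if the rule is applied. If they are withdrawn for missing the 6-month visit, they also have no 6-month clinic reading, so the model has little more than baseline and arm to work with.

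**Whether the record back-up restores the outcome.** Consent is described for patients who withdraw, when disengaged patients are least likely to sign. The stated use is a comparison with completers. Routine record readings are not the defined endpoint, the average of three telemonitor readings at the study visit. So as written it does not restore the outcome.

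**Possible size (arm-specific rates and gaps are assumptions).** Let d be the dropout proportion in an arm and w the amount by which dropouts' 12-month SBP change is worse than completers'. The completer mean equals the all-patient mean minus d × w, so a completers-only contrast is off by (d1 − d3) × w when w is the same in both arms:

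- 25% vs 15%, w = 5: 0.10 × 5 = 0.5 mm Hg; w = 10: 1.0 mm Hg.
- 30% vs 10%, w = 10: 0.20 × 10 = 2.0 mm Hg.
- 20% vs 20%, same w: 0.

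The range 0.5 to 2.0 mm Hg is 7% to 29% of 7 mm Hg. It understates the Group 3 benefit; the sign reverses if Group 1 dropouts do better than those who stay.

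**What a missing-at-random analysis does.** A simulation used 400,000 patients per arm, a true difference of about −7 mm Hg, SD 14 at 6 months and 16.5 at 12 months, correlation 0.6, and dropout of about 30% in Group 1 and 8% to 10% in Group 3. Missing 12-month changes were predicted within arm from the 6-month change.

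| Dropout depends on | True | Completers only | Missing at random |
|---|---|---|---|
| Arm only | −6.92 | −6.93 | −6.95 |
| Arm and observed 6-month value | −7.00 | −5.65 | −6.98 |
| Arm and unobserved 12-month value | −6.97 | −4.28 | −5.17 |

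Only the third pattern biases the missing-at-random result, here by 6.97 − 5.17 = 1.80 mm Hg towards no effect.

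**The case against.** The strongest reply is that leaving study follow-up is not the same as leaving the analysis. The Withdrawal section nowhere removes anyone from the analysis set, intention-to-treat is stated twice, and a mixed model with multiple imputation is planned. This stands. A reader might infer that the text contradicts intention-to-treat; it does not. The rule conflicts with the aim because it makes outcomes missing, not because it excludes patients.

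The criterion is also unwillingness, with non-attendance as an example, and no number of missed visits triggers it. A reader might infer automatic withdrawal after a missed visit; the text does not say so.

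A third inference is that allocation-driven dropout invalidates the missing-at-random assumption. The first two simulation rows show that it does not when arm is in the model. The Discussion says only that such bias may occur, and does not say that loss depends on unobserved BP.

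The comparison of withdrawn patients with completers deserves credit: it is an empirical check on whether dropouts do worse. Many who leave may also remain reachable as registered patients of their health centre. Neither point puts a 12-month value into the primary comparison. Sensitivity analyses that depart from missing at random may sit in the promised SAP, so their absence here is no finding.

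**Conclusion.** The concern holds in a limited form. Criterion (2) can cost the primary outcome of patients who would still have supplied it, against the plan's own aim of complete data, and the record back-up is too weakly tied to the analysis to make good the loss. The rule is stated text, not missing detail, and its effect cannot be undone once follow-up ends.

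The size cannot be fixed from the document. The 0.5 to 2.0 mm Hg range is not the bias of the planned analysis. It describes a completers-only comparison under assumed dropout by arm and an assumed gap of 5 to 10 mm Hg. The planned model carries only the part that depends on unobserved BP within arm. That part is zero if dropout and the remaining gap are equal in both arms. Under the assumed pattern it understates the Group 3 benefit, so the main risk there is a missed effect, not a false positive.

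**What to change.** - **Follow-up.** Remove criterion (2) as a ground for ending study follow-up. Record missed visits or tests as protocol deviations, and still seek the 12-month BP unless the patient withdraws consent. This concerns outcome collection only, not treatment.
- **Consent.** Obtain consent for record retrieval at enrolment. Trial status describes the study as ongoing, so ask patients already enrolled as well.
- **Use of record data.** Use the 12-month BP from the health record in a sensitivity analysis for patients without a 12-month study reading, in addition to the comparison with completers.
- **Optional, for the SAP.** A delta-adjusted imputation by arm would show how far results depend on missing at random.

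The cost is some reminder effort, rewording of the protocol and consent form, and one sensitivity analysis. Record readings are less standardised than the study measurement, which is why they should not enter the primary analysis. The sample size of 330 does not change.
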